#### Blinding

Due to the nature of the intervention, blinding of patients and nursing staff to allocation is not feasible. However, the staff responsible for discharge decisions are not informed that PACU length of stay is the primary outcome. They are informed that delirium incidence assessed by the NUDESC score is the primary study endpoint. Discharge decisions are made according to routine clinical practice. Data are collected at the bedside by a doctoral researcher and entered directly into the electronic case report form. The researcher is unaware of the primary outcome.

### Statistical considerations and methods

#### Sample size

The primary outcome is length of stay in the post-anesthesia care unit (PACU), measured in minutes. As this is an exploratory study, no prior interventional data were available to inform the expected effect size. From an organizational perspective, a reduction of 5% in PACU length of stay was defined as the minimal relevant effect. Given a daily throughput of approximately 35–40 patients and responsibility for 16 operating rooms and additional anaesthesia workplaces, even small reductions in average PACU length of stay may translate into a meaningful cumulative gain in PACU capacity and potentially reduce operating room delays. Assuming a mean PACU stay of 90 min with a standard deviation of 40 min in the study population, this corresponds to an absolute reduction of 4.5 min and a standardized mean difference (Cohen’s d) of 0.11. The assumed mean PACU length of stay was derived from institutional administrative data used for nursing staffing and capacity planning. The sample size calculation assumed a two-sided type I error rate of 0.05 and 80% power. Under individual randomization, detecting this effect using a two-sample t-test would require approximately 2,600 patients. Because the study uses cluster randomization by day to avoid contamination, the sample size was inflated to account for within-cluster correlation. Assuming an average of approximately 30 patients per cluster and an intracluster correlation coefficient (ICC) of 0.01, the required sample size increased to 3,140 patients. Recruitment will stop once 3,140 patients with complete datasets have been enrolled; the planned study period is six months.

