## Discussion

In our trial, we test whether ice-lollies offered to patients in the PACU lead to shorter time spent in the PACU until decision to discharge to the general ward. We chose this supportive, cost-effective intervention because it is easily translated into other health care systems, does not require a physician and has presumably no relevant side effects.

We expect faster recovery on days with ice-lollies as intervention for several reasons. First, the cold serves as neuronal thermal sensory stimulus helping to wean off residual sedation. Second, patients focus on hand-mouth coordination for some time, leading to a distraction from negative feelings of boredom and pain. Third, ice-lollies are a relief to the common side effects dry mouth and bitter or metallic taste after anaesthesia. Last, ice-lollies are for many people associated with happy childhood memories, helping to relieve stress symptoms.

If our intervention proves effective in shortening the length of stay in the PACU, this may lead to a smoother and more efficient recovery process for patients after anaesthesia. A reduced stay has the potential to improve the overall patient experience by minimizing discomfort and time spent in a high-monitoring environment, while at the same time preserving safety standards. From a medical-economic perspective, even modest reductions in recovery times can translate into meaningful benefits, including improved operating room throughput, better availability of postoperative recovery beds, and decreased staff workload. Capacity of postoperative recovery is crucial for a well organised OR, since overflow in the PACU lead to delay of subsequent surgeries. (Weissman et al. 2019) Both, physical space and trained staff, are a prerequisite for admission to the PACU. For sample size calculation we conservatively estimated a time reduction of five minutes per patient due to the activating effect of offering ice-lollies. This translates to an additional hour of one nurse per day who can care for three patients, an effect that could ease blocking of OR due to PACU overflow. (Macario et al. 1999) In high-volume surgical settings, these effects may contribute to both enhanced quality of care and more efficient use of healthcare resources.

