### Trial status

Patient recruitment began in July 2025 and is expected to be completed in February 2026. This article is based on the most recent version of the study protocol (V 1.0, 11th June 2025). Publication of the protocol after beginning of recruitment is due to blinding of the primary outcome.

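### The inflation for clustering does not reproduce: 2,600 patients, about 30 per day and an ICC of 0.01 give 3,354, not 3,140, so the stated 80% power is narrowly missed

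*Protocol article*

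**What the plan says.** The Sample size section of the protocol article sets out the calculation for the primary outcome, PACU length of stay.

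- Error rate and power: "The sample size calculation assumed a two-sided type I error rate of 0.05 and 80% power".
- Mean and spread: "Assuming a mean PACU stay of 90 min with a standard deviation of 40 min in the study population".
- Effect: a 5% reduction is taken as the minimal relevant effect, and "this corresponds to an absolute reduction of 4.5 min and a standardized mean difference" of 0.11.
- Individual randomisation: "detecting this effect using a two-sample t-test would require approximately 2,600 patients".
- Clustering by day: "Assuming an average of approximately 30 patients per cluster and an intracluster correlation coefficient (ICC) of 0.01, the required sample size increased to 3,140 patients".

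No other inflation or reduction is stated. There is no allowance for dropout, since the target counts complete datasets, and no variance reduction from covariates is used. The figure 3,140 also appears in the abstract and under Trial design, and it is the recruitment target.

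The Discussion describes the effect differently: "For sample size calculation we conservatively estimated a time reduction of five minutes per patient".

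**The concern.** Every input to the clustering step is printed, so a reader can check it, and the check fails. The first step (2,600) follows from the stated effect size. The second step (3,140) does not follow from the first. The reader cannot tell whether the cluster size, the ICC, the effect size or the final figure is the one that differs from what was really used. The Discussion adds to the doubt by attributing a different effect to the same calculation.

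The stake is how the primary result will be read. If the trial finds no difference, its planned power for 4.5 min is the yardstick, and under the printed assumptions that power is not quite 80%. The article also offers itself as a template for similar studies, so a reader may copy the step.

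**Working it through.** **Inputs** (all from the Sample size section): two-sided alpha 0.05; power 80%; SD 40 min; effect 4.5 min, stated as d = 0.11 (unrounded 4.5/40 = 0.1125); m = 30 patients per day; ICC = 0.01. Allocation of days is 1:1 (Protocol section).

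**Step 1: individual randomisation.** Total N = 4 × (1.96 + 0.8416)² / d², rounded up per arm.

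- d = 0.11: 2,596 (2,598 with the exact t-test). This reproduces the stated figure of about 2,600.
- d = 0.1125: 2,482 (2,484 with the exact t-test). This is not the stated figure.

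**Step 2: inflation for clustering.** Design effect DE = 1 + (m − 1) × ICC = 1 + 29 × 0.01 = 1.29.

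- 2,600 × 1.29 = 3,354.
- Printed: 3,140. Difference: 3,354 − 3,140 = 214, and 214/3,354 = 6.4%.

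**Step 3: what 3,140 would imply.** 3,140/2,600 = 1.208. At ICC 0.01 this needs m = 1 + 0.208/0.01, about 22 per day. At 30 per day it needs ICC = 0.208/29, about 0.0072. The article states neither.

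**Step 4: other readings tried.**

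| Reading | Resulting N |
|---|---|
| DE = 1 + m × ICC = 1.30, from 2,600 | 3,380 |
| Unrounded d = 0.1125: 2,482 × 1.29 | 3,202 |
| Effect of 5 min (d = 0.125): 2,010 × 1.29 | 2,593 |
| One-sided alpha, d = 0.1125: 1,954 × 1.29 | 2,521 |
| One-sided alpha, d = 0.11: 2,044 × 1.29 | 2,637 |

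None gives 2,600 and 3,140 together. The unrounded effect comes closest to 3,140, at 3,202, but its unclustered size is 2,482 and not 2,600.

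**Step 5: power at 3,140 with m = 30 and ICC 0.01.** Effective N = 3,140/1.29 = 2,434. Power = Φ(d × √(2,434/4) − 1.96).

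- d = 0.11: Φ(2.714 − 1.96) = 77.4%.
- d = 0.1125: Φ(2.775 − 1.96) = 79.3%.
- With a t reference on about 103 cluster degrees of freedom (3,140/30 ≈ 105 days, less 2), these become 76.7% and 78.5%.

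Put the other way, the difference detectable with 80% power is (1.96 + 0.8416) × √(4 × 1.29/3,140) × 40 = 4.54 min, against the planned 4.5 min.

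**Step 6: the Discussion.** Five minutes is d = 5/40 = 0.125. It is a larger effect than 4.5 min, so it is not the more cautious choice, and with the same design effect it needs only 2,593 patients. It cannot be the source of 3,140.

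**The case against.** The strongest reply is that the shortfall hardly matters. The minimal relevant effect is 4.5 min, which is d = 0.1125; the value 0.11 is a rounding that corresponds to 4.4 min. On the exact effect, 3,140 is within 2% of the required 3,202 and power is 79.3%. The cluster size is only approximate, and at 27 per day the same effect has 80.2% power. The planned model also adjusts for age, sex, ASA status, surgery type, and duration and type of anaesthesia. Covariates explaining about 2% of the variance (for d = 0.1125) or 6.4% (for d = 0.11) would restore 80%. All of this stands as to size. It does not make the printed step right: the calculation does not invoke covariates, the explained variance is an assumption, and the unrounded effect contradicts the stated 2,600.

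A reader might infer more than the article supports, in five ways.

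- **Serious underpowering.** The loss is 0.7 to 2.6 percentage points before adjustment, which does not support that description.
- **Still lower power at 35–40 patients per day.** That figure is the unit's daily throughput, given in the capacity argument. The Patients section restricts specialties and excludes some patients, and the stated cluster size is about 30.
- **A fault in stopping on a patient count.** Power depends on both patients and days. If fewer patients arrive per day, reaching 3,140 takes more days and power rises.
- **A wrong nurse-hour claim in the Discussion.** It reproduces from throughput: 40 × 4.5 / 3 = 60 min.
- **About 22 per day as the true planning value.** The Trial status section says "Patient recruitment began in July 2025 and is expected to be completed in February 2026", longer than the planned six months, so daily accrual may be below 30. But the article gives no number of study days, and choosing 22 because it yields 3,140 fits the assumption to the answer.

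**Conclusion.** The concern holds as an internal inconsistency in the sample size calculation with a small effect on power. On the printed inputs the required size is 3,354, and 3,140 is 6.4% short of it. The trial then has about 77% power for d = 0.11 and about 79% for d = 0.1125, not 80%. These figures assume the usual design effect with equal cluster sizes, SD 40 min, ICC 0.01, 30 patients per day and no gain from covariates. The five-minute figure in the Discussion is a separate, minor mismatch with the 4.5 min in the Sample size section. Design, analysis model and primary outcome are unaffected. The point should be fixed, but it does not threaten the trial.

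**What to change.** Keep 3,140 and correct the text in one of two ways.

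1. Keep 30 per day and ICC 0.01, and state that 3,140 patients give about 77% power for d = 0.11 or about 79% for d = 0.1125, before covariate adjustment.
2. If other inputs were used at planning, state the effect size (with enough decimals), cluster size and ICC, and show the steps that lead from them to 3,140. These should be the planning values and not values chosen to match observed accrual.

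In the Discussion, replace the five-minute figure with the 4.5 min used in the Sample size section.

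The cost is wording only: no extra patients and no change to the analysis. Under the first option the stated power becomes slightly less favourable.

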#### Statistical analyses

After patient enrolment is finished, data will be analysed. There is no interim analysis planned due to the short study period. Patient characteristics and clinical data will be descriptively analysed as appropriate after visual normality check. The proportion of missing data is expected to be very low, as data are entered prospectively at the bedside by a dedicated study investigator. If missing data remain minimal, a complete-case analysis will be performed. If the proportion of missing data should exceed expectations, appropriate sensitivity analyses will be considered. The analysis will be conducted as Intention-to-Treat (ITT) in all randomized patients according to group assignment and Per-Protocol (PP) with all patients who received the assigned intervention as planned. All tests will be two-sided, with α = 0.05.

Baseline characteristics will be summarised descriptively by treatment group. Continuous variables will be reported as mean (standard deviation) or median (interquartile range), as appropriate. Categorical variables will be presented as counts and percentages. No formal statistical testing of baseline differences will be performed.

To account for the cluster-randomized design with randomization at the level of the day, all inferential analyses will be performed using mixed-effects regression models including a random intercept for cluster (day).

For the primary outcome (PACU length of stay), a linear mixed-effects model will be used. If substantial deviation from normality is observed, an appropriate generalized linear mixed-effects model (e.g., gamma distribution with log link) will be applied. Binary outcomes will be analysed using generalized linear mixed-effects models with logit link.

For medication dosage outcomes with a high proportion of zero values, a two-part modelling approach will be applied: first, a mixed-effects logistic regression model will analyse the probability of receiving any medication (yes/no); second, among patients receiving medication, dosage will be analysed using an appropriate mixed-effects model depending on distributional characteristics.

For the primary and secondary outcomes, age range, sex, ASA physical status, surgery type, and duration and type of anaesthesia will be included as covariates. For the secondary outcomes pain medication and nausea/vomiting, the duration of stay in the PACU is included as an additional covariate.

Prespecified subgroup analyses are performed based on age (≤ 12 years and ≥ 75 years), sex, ASA classification, type of anaesthesia and surgery type (neurosurgery, orthopaedic surgery, ENT, plastic surgery). Subgroup analyses are considered exploratory.

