Every morning, the study day is randomised via a web-based randomisation tool (studyrandomizer.com, Rotterdam, Netherlands).(Study Randomizer 2017) Study days are randomized in a 1:1 ratio using permuted blocks with variable block sizes ranging from 2 to 6. The researcher collecting the data is blinded to randomisation details (e.g., blocking). On intervention days, ice-lollies are offered to all eligible patients by the nursing staff in addition to standard of care refreshments at the same time point at which oral fluids are routinely offered, and always at nurse discretion. Patients must be sufficiently awake and able to safely hold and swallow oral intake. No formal recovery score threshold is applied. On control days there is standard of care without ice-lollies. Standard postoperative refreshments in our institution include water, coffee and biscuits. Nurses are notified of the randomisation result by personal communication and a large sign in the middle of the PACU. To ensure protocol adherence and prevent cross-contamination, the freezer is kept securely locked on control days when no ice-lollies are provided. Adherence to the intervention will be documented. On intervention days, it will be recorded whether an eligible patient was offered and consumed an ice lolly. Patients who decline the ice lolly despite being eligible will remain in the intention-to-treat analysis according to the randomized day. A per-protocol analysis will additionally be performed including only patients who received the allocated intervention as planned. Anonymised patient data is entered prospectively at the bedside by a dedicated study investigator directly into a password-protected electronic Case Report Form (eCRF) hosted on the secure intranet server. Access is restricted to the research team and all activities are logged. No direct personal identifiers (e.g., name, hospital number, case number) are recorded. K-anonymisation is ensured by generalization via binning (age, height, weight, procedure) in predefined ranges. Data completeness is monitored during entry with immediate correction of missing or implausible values. Data collection ends when the patient is discharged to the general ward without follow-up. Patients are not re-identifiable in the study database.

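### Days are randomised in small calendar blocks, but the stated model has no calendar-time term; if length of stay drifts, the interval is conservative and some precision is given away at no benefit

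*Protocol article*

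**What the plan says.** **Allocation (Protocol article, Protocol).** Allocation is sequential: "Every morning, the study day is randomised via a web-based randomisation tool". It is also restricted: "Study days are randomized in a 1:1 ratio using permuted blocks with variable block sizes ranging from 2 to 6". Each completed block holds equal numbers of intervention and control days, so the arms stay balanced as the calendar advances.

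**Duration (Trial status).** "Patient recruitment began in July 2025 and is expected to be completed in February 2026". The trial therefore spans summer, autumn and winter.

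**Analysis (Statistical analyses).** All inferential analyses use "mixed-effects regression models including a random intercept for cluster (day". For the primary and secondary outcomes, "age range, sex, ASA physical status, surgery type, and duration and type of anaesthesia will be included as covariates". Two secondary outcomes also take PACU stay as a covariate. No study day, month, period or randomisation block appears.

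**The concern.** A random day intercept treats the days as exchangeable. If length of stay moves gradually over the recruitment months (season, staffing, practice), that movement is absorbed into the between-day variance and so into the standard error of the treatment effect. Blocking, however, has forced both arms to sample nearly the same stretch of calendar, so the movement hardly contributes to the real sampling variation of the effect. The model then reports more uncertainty than the design has. At stake is precision in a trial sized for a small effect (4.5 min) with no spare power. Neither the validity of the test nor the estimate is in question.

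**Working it through.** **Inputs (Sample size section).** "Assuming a mean PACU stay of 90 min with a standard deviation of 40 min in the study population"; effect, "an absolute reduction of 4.5 min and a standardized mean difference (Cohen’s d) of 0.11"; "The sample size calculation assumed a two-sided type I error rate of 0.05 and 80% power"; 30 patients per day; ICC 0.01; total 3,140.

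**The plan's own figure.** Per arm, n = 2(1.96 + 0.84)² × 40² / 4.5² ≈ 1,241, so 2,482 in total. The design effect is 1 + 29 × 0.01 = 1.29, and 2,482 × 1.29 = 3,202. The stated 3,140 is about 2% lower and gives about 79.3% power. (The stated 2,600 follows from d rounded to 0.11, which gives 2,596; 2,600 × 1.29 = 3,354, so the two printed totals do not come from one chain. This does not affect the present point.) The number of days is 3,140 / 30 ≈ 105.

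**Standard error without drift.** Between-day variance is 0.01 × 1,600 = 16. The variance of a day mean is 16 + 1,584/30 = 68.8. SE = 2√(68.8/105) = 1.619 min.

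**Effect of drift.** A linear drift of D minutes over the trial adds D²/12 to the variance between day means. The planned model counts it; the blocked contrast does not. With the critical value c = 1.983 (103 df),

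power ≈ Φ[(4.5 − c × model SE) / true SE].

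There are two ways to combine an assumed drift with the planned ICC:

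- *On top:* 0.01 is the residual ICC and drift is extra. For D = 10, model SE = 2√((68.8 + 8.33)/105) = 1.714; true SE stays 1.619.
- *Within:* 0.01 is the total ICC and drift is part of it. For D = 10, model SE = 1.619; true SE = 2√((68.8 − 8.33)/105) = 1.518. The between-day variance of 16 leaves room for D up to √(12 × 16) ≈ 14 min.

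| Assumed linear drift | Model SE, planned | True SE | Power, planned | Power with time term |
|---|---|---|---|---|
| none | 1.619 | 1.619 | 78.7% | 78.7% |
| 5 min, on top | 1.643 | 1.619 | 77.8% | 78.7% |
| 10 min, on top | 1.714 | 1.619 | 75.2% | 78.7% |
| 10 min, within | 1.619 | 1.518 | 80.2% | 83.7% |
| 13 min, within | 1.619 | 1.444 | 81.4% | 87.1% |

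**Simulation check.** The set-up was 105 days of 30 patients with permuted blocks of 2/4/6 and analysis of day means, which is equivalent to the random-intercept model when cluster sizes are equal. The main run had 6,000 trials per scenario (Monte Carlo error √(0.78 × 0.22/6,000) ≈ 0.5 points; both models were fitted to the same data). Planned model against model with linear study day:

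- No drift: 78.7% vs 78.5%.
- 5 min on top: 77.3% vs 78.1%.
- 10 min on top: 75.7% vs 79.4%, with type I error 3.7% vs 4.8%; a separate run gave 75.0% vs 78.5%, with 4.0% vs 4.8%.
- 10 min within: 79.6% vs 82.7% in one run, 80.1% vs 83.9% in another.
- 13 min within: 81.1% vs 87.1%.

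**Shape of drift.** A straight line is not enough. For a 10 min V-shape on top, power was 74.5% planned and 74.6% with a linear term. For a 10 min seasonal wave it was 71.6% and 71.5%. Terms with 3 to 4 df gave 77 to 78% in both. How much a line recovers from a seasonal wave depends on its phase: another 20 min wave gave 56.7% planned, 69.6% linear and 78.5% with a five-term polynomial.

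**Cost with no drift.** A 3 to 4 df term costs about 0.3 to 0.6 points.

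**The case against.** The strongest reply is that nothing is broken. The random intercept matches the unit of randomisation, the estimate is unbiased, and the type I error is at or below 5%. All of that stands.

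Second, no passage gives or suggests a trend in length of stay. With no drift there is no loss. This stands, and it makes every figure conditional.

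Third, a reader might infer that the trial will miss its planned 80% power. The documents do not support that. The planned ICC of 0.01 describes all correlation within a day, and drift is part of it. Placing drift on top raises the total ICC above the planning value: (16 + 8.33)/1,600 ≈ 0.015 at 10 min and (16 + 18.75)/1,600 ≈ 0.022 at 15 min. Larger losses, such as about 70% power at 15 min, therefore describe a trial with more than twice the planned ICC. With the total held at 0.01, the planned model keeps about 80%.

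Fourth, the covariates may already absorb drift that comes from case mix. The calculation has no covariates and gives no credit for this.

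Fifth, the analysis plan is not shown and could contain a time term. The article says that its listed covariates will be included, not that others are barred. The point concerns the model as stated; if the analysis plan already has such a term, nothing remains to be done.

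Sixth, a random intercept needs only a day label. The article describes binned, anonymised data and does not say that calendar order is stored. This also stands and must be checked.

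None of this removes the mechanism: the stated model does not use the balance over time that the randomisation creates.

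**Conclusion.** The point holds as forgone efficiency and as a free improvement, not as an error in the plan. If length of stay drifts beyond what the covariates explain, the planned interval is conservative. The price is about 1 point of power for a 5 min linear drift on top of ICC 0.01 and about 3 to 4 points for 10 min. If the ICC of 0.01 already contains the drift, planned power is met, and the gain forgone is about 3 to 4 points at 10 min and about 6 at 13 min.

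These sizes rest on an assumed drift, equal clusters of 30 and a normal primary outcome; the loss for the secondary outcomes was not computed. A reader might also infer that one linear study-day term settles the matter. It does so only if the drift is roughly linear.

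**What to change.** Before the data are analysed, prespecify study-day order as a flexible fixed effect with few degrees of freedom, for example a spline with 3 to 4 df, in the primary and secondary mixed models. Carry it into the gamma or logit version where that is used. Keep the random day intercept. Do not rely on a straight line alone.

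The cost is at most about 0.6 points of power if there is no drift. No extra patients or measurements are needed. One condition must be confirmed: that the order of study days is kept in the anonymised dataset, or can be linked to the anonymised day label, for example from the sequence of daily allocations.

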#### Secondary outcome

Three secondary outcomes have three main components: pain, nausea and vomiting, and delirium. Pain includes the visual analogue scale at admission and discharge, and consumption of pain medication such as opioids, NSAID, metamizole and paracetamol. Nausea and vomiting is documented as separate outcomes, in addition the administration of any antiemetic medication intra- or postoperatively is recorded. Delirium is defined as a Nursing Delirium Screening Scale (NUDESC) at discharge ≥ 2. The NUDESC is also the communicated primary outcome to the staff and study team involved in data collection.

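### Where medication doses have many zeros, dose is compared only among recipients, a group formed after randomisation, and no planned result estimates the amount consumed per patient

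*Protocol article*

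**What the plan says.** Under Secondary outcome, the protocol article declares an amount of drug as part of the pain outcome: "consumption of pain medication such as opioids, NSAID, metamizole and paracetamol".

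Under Statistical analyses it sets a conditional rule: "For medication dosage outcomes with a high proportion of zero values, a two-part modelling approach will be applied". The first part is a mixed logistic model for any use, yes or no. The second part reads: "second, among patients receiving medication, dosage will be analysed using an appropriate mixed-effects model depending on distributional characteristics". No estimate that joins the two parts, and no dose contrast over all patients, is named.

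The same section fixes the analysis set: "The analysis will be conducted as Intention-to-Treat (ITT) in all randomized patients according to group assignment". It lists baseline covariates (age range, sex, ASA status, surgery type, duration and type of anaesthesia) and, for pain medication, adds PACU length of stay. Tests are two-sided at 0.05, and the second part is not marked as descriptive.

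Under Protocol, the day is allocated each morning. Under Blinding: "Due to the nature of the intervention, blinding of patients and nursing staff to allocation is not feasible".

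**The concern.** A drug given in the PACU is given after the day has been allocated. Pain medication is an outcome on which the trial looks for an effect, so whether a patient becomes a recipient may depend on the arm. If it does, recipients on lolly days and recipients on control days are different kinds of patient, and a difference in their mean dose mixes any change in dosing with a change in who is dosed. The listed baseline covariates do not remove this, because analgesic need drives the selection and they capture it only in part.

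At stake is the reading of one declared secondary outcome. If the first part shows fewer users and the second a higher dose among users, the plan names no result that says whether the amount consumed fell. A reader could take the second part as evidence that lollies raise analgesic dose.

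**Working it through.** **Inputs.** The article states no share of patients medicated and no dose, so there is no figure of its own to reproduce. The structure (two parts, recipients only in the second, days allocated 1:1) comes from Statistical analyses and Protocol. All usage and dose figures below are assumptions.

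**1. General condition.** Let a share p of control patients use the drug, with mean dose μ. Let the lolly spare a share q of all patients, whose mean dose would have been d, and change nobody else.

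- Users-only mean on lolly days: (pμ − qd)/(p − q)
- Mean per patient on lolly days: pμ − qd

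The users-only mean exceeds μ exactly when pμ − qd > pμ − qμ, that is, when d < μ. Mean consumption per patient falls by qd whatever d is.

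**2. Numbers.** Take p = 0.50 and μ = 6 mg, so control consumption is 0.50 × 6 = 3.00 mg per patient.

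| q | d (mg) | Users-only mean (mg) | Change | Per patient (mg) | Change |
|---|---|---|---|---|---|
| 0.05 | 3 | (3.00 − 0.15)/0.45 = 6.33 | +5.6% | 2.85 | −5% |
| 0.10 | 3 | (3.00 − 0.30)/0.40 = 6.75 | +12.5% | 2.70 | −10% |
| 0.05 | 6 | (3.00 − 0.30)/0.45 = 6.00 | 0% | 2.70 | −10% |
| 0.05 | 9 | (3.00 − 0.45)/0.45 = 5.67 | −5.6% | 2.55 | −15% |

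Depending on who is spared, the users-only contrast points the wrong way, shows nothing, or shows too small a fall.

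**3. Counter-case: need falls in everyone.** Let need be normal with SD 1 and mean m. The drug is given when need exceeds 0, and dose is proportional to need.

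- Users-only mean: m + φ(m)/Φ(m)
- All-patient mean: mΦ(m) + φ(m)

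With 50% users (m = 0) and a fall of 0.1 SD, the users-only mean goes from 0.798 to 0.763 (ratio 0.96). The share of users goes from 0.500 to 0.460. The all-patient ratio is (0.460 × 0.763)/(0.500 × 0.798) = 0.88.

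Over 30%, 50% and 70% users and falls of 0.1 and 0.2 SD, the users-only ratio is 0.91 to 0.96 and the all-patient ratio 0.72 to 0.91. If every user's dose also contains a fixed minimum equal to 1 SD of need, the ranges are 0.95 to 0.98 and 0.76 to 0.93. The direction is right here, but the users-only contrast understates the fall.

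**4. At about the trial's size.** The simulation used 104 days of 30 patients, 1:1 by day, with 200 replicates. It used a linear model with day-clustered standard errors, no covariates and no day effect on dose. Of all patients, 25% were mild-pain users (mean 3 units) and 25% severe-pain users (mean 9 units). The lolly spared some mild-pain users and changed no other dose.

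| Mild-pain users spared | Significant users-only increase | Significant all-patient decrease |
|---|---|---|
| 0% | 3.5% | 3% |
| 10% | 13% | 8.5% |
| 20% | 43% | 21% |
| 40% | 97% | 60% |

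The 20% and 40% rows correspond to q = 0.05 and q = 0.10 with d = 3 in step 2. In this scenario the misleading signal is detected more often than the true one.

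**The case against.** The strongest reply is that the model itself is not at fault. A two-part model is a normal choice for doses with many zeros, and the combined mean is simply the product of its two outputs. A statistical analysis plan is said to be available on request and may report it. That is fair as to the combined estimate. It does not remove the point, because the article itself fixes the dose contrast among recipients, alongside a promise to analyse all randomised patients, and does not call that contrast descriptive.

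Several stronger readings are tempting, and the document does not support them:

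- *The lolly will appear to raise the dose.* This needs selective sparing of patients with below-average doses. Under a uniform fall in need, as in step 3, the users-only dose falls too. The article also cites an earlier trial in children that found no difference in pain medication given, which suggests that selection into the recipient group may be weak.
- *The analgesic analysis as a whole is invalid.* The first part compares all randomised patients and would pick up fewer users. The rule also applies only where zeros are frequent.
- *Unblinded nurses select who is medicated.* Nursing staff know the allocation, but the article does not say who decides on analgesia, nor does it call these drugs rescue treatment.
- *All PACU analgesia is open to the effect.* The lolly is offered when oral fluids are, so eating it cannot change drugs given earlier.

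The consequence is also limited: one part of one secondary outcome, in a study that describes itself as exploratory.

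**Conclusion.** The point holds for medication doses with many zeros. The second part conditions on a post-randomisation event that the intervention may influence, so it is not a randomised comparison and departs from the article's own intention-to-treat commitment. The first part is a valid comparison of any use. Neither part estimates the effect on amount consumed.

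The principle is certain. The size is not, because it rests wholly on assumed usage, doses and pattern of sparing. In the main illustration the users-only dose moves +5.6% against −5% in consumption per patient; other equally assumed patterns give no change or an understated fall. The change is worth making because it is cheap and bears on a declared secondary outcome. The primary outcome, the sample size and the conduct of the trial are not affected.

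**What to change.** Keep the two-part model and add a short paragraph to the analysis text:

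- Report as the treatment effect on consumption, for each drug or drug class, the difference or ratio in mean dose per randomised patient with zeros included: P(any use) × mean dose among users, by arm.
- Standardise it over the baseline covariates only. PACU length of stay should not enter this estimate. It is measured after randomisation and is the primary outcome, so adjusting for it would bring back the same kind of problem.
- Take the confidence interval from resampling whole days, so that clustering is respected.
- Label the dose comparison among users as descriptive and draw no treatment conclusion from it.

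No new data are needed, and the cost is some wording and a little programming. The small drawback is that an all-patient mean is more sensitive to a few high doses.
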